## Abstract

**Background:**

Accidental falls are common among community-dwellers, probably due to the level of physical activity and impaired postural stability. Today, fall risk prediction tools’ discriminative validity are only moderate. In order to increase the accuracy, multiple variables such as highly validated objective field measurements of physical activity and impaired postural stability should be adressed in order to predict falls. The main aim of this paper is to describe the ≥65 years NOrthern jutland Cohort of Fall risk Assessment with Objective measurements (NOCfao) investigating the association between physical activity and impaired postural stability and the risk of fall episodes among community-dwelling older adults.

**Methods:**

The study consists of a baseline session where the participants are asked to respond to three questionnaires, perform physical tests (i.e., measuring strength in the upper and lower extremities, balance, and walking speed), participate in an assessment of pain sensitivity, and to wear an ankle mounted pedometer for measuring physical activity for 5 days. Subsequently, the fall incidences and the circumstances surrounding the falls during the previous 1 to 2 months will be recorded throughout a one-year follow-up period.

**Discussion:**

This study will add to the present-day understanding of the association between physical activity and impaired postural stability and the risk of fall episodes among community-dwelling older adults. These data will provide valid and reliable information on the relationship between these variables and their significance for community-dwelling older adults.

**Trial registration:**

ClinicalTrials.gov identifier: NCT2995317. Registered December 13th, 2016.

## Background

Accidental falls are common in the elderly population [1] with increased risk of falls with increased age and level of fragility [2–5]. Among home-dwelling older adults (≥65 years), 33% will have at least one fall per year [2, 6, 7] with higher prevalence as the age increases (i.e., 40% over 80 yrs) [8–10]. Such accidents cause injuries, fear, and reduced quality of life [11, 12] along with increased morbidity (e.g., higher risk of institutionalization and hospitalization) and mortality [11–13]. Moreover, falls are the most prevalent cause for injury-related deaths among older adults ≥65 years [14]. It is estimated that up to 0.20% of the gross domestic production and 0.85–1.50% of the health care costs are related to fall incidences [15]. With a rapidly growing proportion of individuals over 65 years, this group is projected to represent 15.6% of the world’s population by 2050 [16] constituting both a present and future societal challenge. In summary, the burden of accidental falls among older adults on the individual, family, community, and society is tremendous [2]. Therefore, fall prevention in this population is considered a point of focus in relation to public health globally [17].

Various risk factors, such as muscle weakness, history of falls polypharmacy, gait, and balance deficits increase fall risk [18–20], indicating that both clinical data and technical assessments are important for screening a multifactorial problem such as fall risk [6, 21]. An embedded definition by Tinetti and colleagues (1998) states a fall as: “*an event which results in a person coming to rest unintentionally on the ground or lower level, not as a result of a major intrinsic event, such as stroke, or overwhelming hazard*” [11]. Accidental falls are often classified into intrinsic (e.g. non-accidental causes such as history of falls, age, gender, solitary lifestyle, fear of falling, nutritional deficiencies, cognitive disorders, attenuated vision, balance and gait impairment, and foot problems), extrinsic (e.g. polypharmacy) and environmental (e.g. lighting, footwear, and bumpy and slippery surface areas) risk factors [18, 19, 22, 23]. Intrinsic risk factors such as poor balance or gait impairment are particularly common causes to ‘slip and trip’ which may result in accidental falls among older adults [9, 22, 24, 25].

In general, fall prevention in the older adult population may be divided into three key points; 1) screening methods for identifying individuals at high risk of falling, 2) determining the multiple risk factors for a fall, and lastly, 3) implementing individualized interventions into clinical practice [1, 26]. Numerous studies have proposed different screening tools for fall risk assessment [23, 26–28]. The majority of guidelines on fall risk screening usually include a combination of questionnaire-based screening tools (e.g., fall history, walking difficulties, and balance deficits) and functional tests targeting balance and gait impairments [29]. In order to increase the accuracy, a successful screening tool should consist of multiple variables in order to predict falls [1, 30].

Despite the development of numerous fall risk prediction tools among community-dwelling older adults, the discriminative validity to identify those at risk of falling are only moderate [31–34], and a recent study even found disagreement for screening the risk of falling in older adults between several commonly used fall risk assessment methods [35].

There are indications that physical function and activity are closely associated with falls among older adults [36]. Moreover, there are some indications of the existence of a u-shaped pattern in the level of physical activity and risk of falls where both low and high levels of physical activity are associated with greater risk of falls [22]. This highlights physical activity as a key explanatory variable to falls [36]. Previous studies have used accelerometers to investigate the association between physical activity and falls [37, 38]. However, the technologies used (Activpal and Actigraph) have shown low criterion validity compared to hand tally [39] and Stepwatch [38], respectively. This may be due to the low walking speeds represented in these populations [40], which may constitute issues in data interpretation and thereby questioning the research outcome. In this regard, addressing the exposure of time using highly validated, objective diurnal field measurements of physical activity may provide or alter the conventional associations [36, 41] which have not been addressed in the above-mentioned studies [31–34].

Although multiple factors increase the risk for an accidental fall, deficits in postural stability during gait and balance tasks present especially high odds ratios {OR [Range]) (gait: (2.9 [1.3–5.6]), balance (2.9 [1.6–5.4])}, only exceeded by muscle weakness (4.0 [1.5–10.3])) and history of falls (3.0 [1.7–7.0]) [19]. For example, a previous study demonstrated the predictive value of a decrease in walking speed, probably due postural instability, for indoor falls among older adults (Internal rate of return (IRR) = 1.86) [42]. Additionally, the control of lateral stability during standing was associated with increased risk of falls in an older adult population [43] although, to the knowledge of the authors, no reference cut-off values using postural sway measurements when evaluating fall risks have been proposed in the literature so far.

Despite the large amount of evidence relating falls to different parameters, most of the current validated and objective methods used for assessing fall risks are not easily implemented in clinical practice. A risk assessment tool should be both practical, simple, and feasible in terms of usability but also be highly sensitive to distinguish between those at high and low risk of falling to ensure good discriminate validity and power [44]. The risk assessment tool should be valid and reliable for investigating risk factors for falls but also be based on objective measures of physical activity in combination with selected physical- and psychological risk factors, using a prospective design with reports of falls.

## Methods/design

### Aims

The main aim of this paper is to describe the ≥65 years NOrthern jutland Cohort of Fall risk Assessment with Objective measurements (NOCfao) by investigating the association between objectively measured physical activity and monthly prospective measures of falls over a one-year period among community-dwelling older adults ≥65 years. The ancillary clinical perspective of NOCfao is to develop a clinically applicable fall risk prediction tool (FRPT), based on the level of objectively measured physical activity and selected physical and psychological risk factors.

The main study questions of this prospective, observational cohort study are:
Is physical activity among community-dwelling older adults associated with risk of fall episodes?Does impaired postural stability among community-dwelling older adults increase the risk of falls episodes?

### Study design and setting

This prospective, observational cohort study and data collection was registered in accordance to the current guidelines (FOU-UU-006) at the Danish Data Protection Agency, the local Ethics Committee (N-20160020), and registered at ClinicalTrials.gov (identifier:) NCT02995317. This study protocol on the NOCfao study complies to the SPIRIT statements for defining standard protocol items [45], including the recommendations for trials protocol submissions [46] and the STROBE guidelines for reporting observational studies [47]. The study, is led by the University College of Northern Denmark (Department of Physiotherapy), in collaboration with Aalborg University (Institute of Health Science and Technology) and Aalborg Municipality (Department of Elderly and Health) will be conducted in accordance with the principles of the Declaration of Helsinki [48]. The administrative information on the NOCfao study are given in Table 1.

**Table 1 Tab1:** Administrative information on the NOCfao study

Section/item	ItemNo	Description
Primary Registry and Trial Identifying Number	1	ClinicalTrials.gov identifier: NCT02995317
Date of Registration in Primary Registry	2	December 13th, 2016
Secondary Identifying Numbers	3	The North Denmark Region Committee on Health Research Ethics (N-20160020) The Danish Data Protection Agency (FOU-UU-006)
Source(s) of Monetary or Material Support	4	The study is externally supported by the Trygfonden Foundation (ID: 119365)
Primary Sponsor	5	University College of Northern Denmark, Denmark
Secondary Sponsor(s)	6	Aalborg University, Denmark Aalborg Municipality, Denmark
Contact for Public Queries	7	Master of Rehabilitation, [name]; address: [name]; [contact],[name]; e-mail: [contact]
Contact for Scientific Queries	8	Master of Rehabilitation, [name]; address: [name]; [contact],[name]; e-mail: [contact]
Public Title	9	Who is Falling? – Fall Risk Prediction Among Community-Dwelling Elderly (NOCfao)
Scientific Title	10	The ≥65 Years NOrthern jutland Cohort of Fall risk Assessment with Objective measurements (the NOCfao study)
Countries of Recruitment	11	Denmark
Health Condition(s) or Problem(s) Studied	12	Incidence of falls
Intervention(s)	13	Not applicable
Key Inclusion and Exclusion Criteria	14	Inclusion criteria: home-dwelling, manage body transfer independently, walking ability for at least 10 m with or without assistive devices. Exclusion criteria: progressive neurological or rheumatologically illness, diagnosed vestibular problems, experienced pain in a substantial degree limiting or obstructing everyday living, known uncorrected visual or hearing problems, serious difficulties in speaking, understanding or reading Danish, or cognitive impairment equivalent to Mini Mental State Examination < 23
Study Type	15	Prospective, observational cohort study
Date of First Enrollment	16	December 2016
Target Sample Size	17	600
Recruitment Status	18	Recruiting: participants are currently being recruited and enrolled
Primary Outcome(s)	19	Self-reported number of falls confirmed by monthly phone calls [Time Frame: One year follow-up]
Key Secondary Outcomes	20	History of fall incidences within the past year; differences between objective measures and self-reported level of PA

The minimum amount of trial information (20 items) recommended by the World Health Organization (Version 1.2.1) [49].

### Study population and recruitment process

This study is conducted in Aalborg Municipality at different activity centers in collaboration with care workers, nurses, and staff at the activity centers, all employed at the Department of Elderly and Health, Aalborg Municipality. Various public advertising platforms are selected to draw attention to the study. Information material describing the study is posted in local newspapers, newsletters, social media, and through posters distributed to activity centers in Aalborg Municipality. Furthermore, the project manager arranges briefing meetings with groups of employees to provide clarification of the project regarding inclusion/exclusion criteria and information about the study procedure. Information material and informed consent templates will be distributed to those interested in supporting the recruitment process of the study population.

Participants are eligible for inclusion if they are aged ≥65 years, home-dwelling, able to manage body transfer independently, and with a walking ability for at least 10 m with or without assistive devices. Exclusion criteria are progressive neurological or rheumatological conditions, a diagnosed vestibular problem, current pain condition that significantly limits or obstructs everyday living, known uncorrected visual or hearing problems, not able to speak, understand, and read Danish, or cognitive impairment. Since executive function is related to falls [50–52], and the present study protocol requires the participants to wear accelerometers for several days and to recall fall episodes retrospectively (therefore reducing risk of bias), we decided to only include subjects without significant cognitive impairments. In cases where the experienced tester gauge the participant to be cognitively impaired, the participant is to complete a Mini-Mental State Examination (MMSE). Participants with a MMSE < 23 are to be excluded. Information on the intake of medications that might affect postural balance and/or physical mobility is not collected and thus not considered an exclusion criterion.

Participants satisfying the inclusion and exclusion criteria can be recruited in three different ways:
Through employees at activity centers in Aalborg Municipality. The employee contacts the participant directly at the center or by phone and hand out information material. Date, time and place for the baseline tests are arranged in collaboration with the project manager.The employee gives the name and phone number of the participants to the project manager who then arranges the date, time and place for baseline testing with the participant.Participants can make contact to the project manager directly by phone or e-mail. Information material is sent by e-mail or given verbally over the telephone to ensure that the participant fully understands what it takes to participate. Subsequently, an appointment for the time and place for completion of the baseline data is made.

The included participants are arranged in groups and baseline testing will take place at an activity center nearby their home. On this day, information regarding the study procedure is provided and informed written consent is obtained in order to make sure that the participants fully understand the requirements of participation. An overview of the recruitment procedure is illustrated in Fig. 1.

**Fig. 1 Fig1:**
[figure not shown]
Illustration of the recruitment flow of the NOCfao study

### Statistical analyses and sample size justification

Descriptive statistics (e.g., mean, standard deviations, and range) will be performed in order to describe the study population characteristics. Inferential statistics (e.g., t-tests and ANOVAS) will be applied to explore any significant differences between non-fallers, fallers and multiple fallers. Regression and correlation analysis will be undertaken to identify candidate variables (e.g., when combined and/or adjusted) that are significantly associated with falls. Relative risks will be calculated to quantify the association between candidate variables (physical activity and postural sway) as well as psychological factors, fall incidence, socio-demographic data, health information, physical tests, pain sensory profile, and risk of falls between groups. Estimates and confidence intervals will be reported accordingly.

All statistical analyses will be performed using SPSS Statistics software (IBM, Inc., Zurich, Switzerland), STATA (StataCorp, College Station, Texas, USA), Statistica (StatSoft, Inc. (2011). STATISTICA (data analysis software system), version 10. www.statsoft.com.) or MATLAB (The MathWorks Inc., Natick, Massachusetts, USA) and a significance level of 5% will be used for statistical significance. All future statistical reporting from the NOCfao study will follow the Strengthening the Reporting of Observational studies in Epidemiology (STROBE) statement [﻿47﻿].

The size of the study population was estimated based on previous studies on objective measures of physical activity (exposure) and self-reported fall incidence by telephone interview (outcome). Various Danish studies and cohorts have used diurnal recordings of physical activity with accelerometers [53, 54], including the NOMAD study and the DPhacto cohort. Depending on the specific aim of studies from these cohorts, the number of included participants varies from *n* = 198 [﻿55﻿], *n* = 457 [﻿56﻿] and up to *n* = 657 [﻿57﻿]. Among community dwelling older adults aged ≥65 years, approximately one third falls at least once a year [2, 6, 7]. The sample size in studies on fall incidence using telephone interviews have used samples of *n* = 326 and *n* = 331 participants [﻿58﻿, 59]. The assumed number of participants needed at various stages in the recruitment flow from the first contact to complete follow-up data are inspired and modified from the DPhacto protocol paper [﻿53﻿] and are illustrated in Fig. 1. Thus, based on previous studies on both the exposure and outcome, it is estimated that a sample of 600 participants is needed for baseline and 450 participants with complete baseline and follow-up data.

### Data collection

The NOCfao-study is a prospective cohort study with a one-year follow-up of falls using frequent reports of fall incidence, see Fig. 2 and Table 2.

**Fig. 2 Fig2:**
[figure not shown]
The NOCfao study timeline

**Table 2 Tab2:** Assessment overview of the timing and content in the NOCfao study

Domain	Type of Assessment	Notes	BL	DM	FU		Origin
Demographic data	Age	Self-reported	x				
	Gender	Self-reported	x				
	Height	Measured in centimeters	x				
	Weight	Digitally measured on forceplate	x				
	Marital status	Self-reported	x				
	Type of dwelling	Self-reported	x				
	Use of mobility aids	Self-reported	x				
	Use of homecare	Self-reported	x				
Health information	Chronic diseases	Self-reported	x				
	Number of prescribed medications	Self-reported	x				
	Fluid intake	Self-reported	x				
Physical activity	Objectively measured physical activity	Pedometer (Stepwatch3), Repeatedly over 5 days		x			[60, 61]
	Self-reported physical activity	IPAQ-elderly	x				[﻿62﻿]
Pain sensory profile	Muscle tissue	Pressure Pain Threshold	x				[﻿63﻿]
	Severity and duration of pain	Self-reported obtained by NRS	x				[﻿64﻿, 65]
	Location of pain	Body chart	x				[﻿66﻿]
Physical tests	Walking speed	10 m walking test	x				[﻿67﻿, 68]
	Muscle strengths in lower extremities	30-s sit-to-stand	x				[﻿69﻿]
	Muscle strengths in upper extremities	Seehan digital Hand grip dynamometer	x				[﻿70﻿, 71]
	Balance	Force plate measures	x				[﻿72﻿]
		Mini-BESTest	x				[﻿73﻿, 74]
Psychological factors	Anxiety of falling	Falls efficacy scale - International	x				[﻿75﻿]
Fall incidence	Fall incidence and fall circumstance	Phone-interview on a monthly basis. Prospective 1 year			x		[﻿76﻿]
	Fall history	Self-reported one-year history of falls	x				

Notes: *BL*: Baseline; *DM*: Diurnal measurements; *FU*: Follow-up

In order to collect baseline data, individuals included in the study are asked to:
Complete three questionnaires to describe: the characteristics of the cohort, health information, history of falls, anxiety of falling, and self-reported PAPerform physical tests measuring strength in the upper and lower extremities, balance, and walking speedParticipate in assessment of pain sensitivity by recordings of pressure pain threshold (PPT)Wear an ankle mounted pedometer (Stepwatch 3) for measuring activity for five consecutive days

Baseline data, application and use of the activity monitor are supervised by physiotherapy students under the guidance of an experienced physiotherapist. The students receive training through several workshops to ensure high reliability in the test procedure.

To monitor fall incidences, the project manager or students contact participants on a monthly basis by phone throughout the year after recruitment. The numbers of fall incidences during the previous 1 or 2 months are collected, and the circumstances surrounding the falls are registered. The baseline data will be collected between the autumn of 2016 and the end of autumn 2019, and follow-up data between the autumn of 2017 and 2020 (see Table 2).

Data in paper form collected at baseline are physically stored in locked cabinets in a room with an electronic lock complying with the Danish Data Protecting Agency and Institutions guidelines. All data will be entered electronically and stored in a secured database.

In terms of confidentiality data will be identified by a coded ID number. All records that contain names or other personal identifiers, such as locator forms and informed consent forms, will be stored separately from study records identified by code number.

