### Fall incidence

Fall history of the participants are measured retrospectively as a 12-month recall of falls at baseline. Prospective falls are ascertained over a 12-month period by monthly phone calls with the purpose of determining both the number of falls, why the fall occurred, where it occurred, and when during the day the fall incidence happened. Falls are listed as number of falls and expressed in groups: fallers, non-fallers and multiple fallers along with fall rate per person in a year. This is in accordance with international recommendations [﻿84﻿].

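### Students supervise the baseline balance tests, students or the project manager collect the falls by phone, and the article states no masking of callers to baseline results

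*Protocol article*

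**What the plan says.** The article names the staff on both sides of the association.

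- **Exposure side.** Data collection: "Baseline data, application and use of the activity monitor are supervised by physiotherapy students under the guidance of an experienced physiotherapist". Per Table 2, the baseline session covers the Mini-BESTest, force-plate balance, walking speed, sit-to-stand, fear of falling and the one-year fall history.
- **Outcome side.** The same section: "the project manager or students contact participants on a monthly basis by phone throughout the year after recruitment". Table 1, item 19, defines the primary outcome as "Self-reported number of falls confirmed by monthly phone calls". Under Fall incidence, the calls serve for "determining both the number of falls, why the fall occurred, where it occurred, and when during the day the fall incidence happened".
- **Training.** "The students receive training through several workshops to ensure high reliability in the test procedure". The fall interview is not mentioned.
- **Project manager.** One recruitment route passes the participant's details to the "project manager who then arranges the date, time and place for baseline testing with the participant". No testing role is described.
- **Question at stake.** The second main question under Aims is "Does impaired postural stability among community-dwelling older adults increase the risk of falls episodes".

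Coded ID numbers and separate storage of identifying records are described under Data collection, for confidentiality. The limitations section discusses bias in self-reported activity and selection bias, but not interviewer bias.

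**The concern.** The outcome is a verbal report drawn out by a caller, and it covers the previous one or two months. How firmly the caller prompts, and whether a vague answer is followed up, can affect how many falls are recorded. One extra event can also move a participant between the non-faller, faller and multiple-faller groups.

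If callers prompt more fully when they remember a participant as unsteady, falls are ascertained more completely in the group expected to fall more. Under-reporting that is unrelated to balance would generally weaken an association. Ascertainment that follows the exposure can instead create one, in the direction that the second main question asks about, and a larger sample does not remove it. The monthly phone interview is the only prospective source of falls that the article clearly describes, so no independent record is described against which a caller's leaning could be checked.

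**Working it through.** **1. What the text establishes about roles.**

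| Task | Who, per the article | What follows |
|---|---|---|
| Baseline tests | Physiotherapy students, guided by an experienced physiotherapist | They can see balance and gait performance |
| Monthly fall calls | Project manager or students | The student group appears in both tasks |
| Arranging baseline sessions | Project manager, among others | No testing role stated |
| Coded IDs, separate identifiers | Given for confidentiality | Does not remove what a tester saw in person |

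The overlap shown is of a staff category. Baseline runs from autumn 2016 to autumn 2019 and follow-up to 2020, so the callers may or may not be the students who tested a given participant.

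**2. Which exposures are visible to a tester.** Mini-BESTest performance, walking and general unsteadiness are seen directly. Force-plate sway is extracted afterwards from filtered data by a MATLAB script (Balance section). Step count comes from an ankle device worn over five days (Physical activity section). The route to bias is therefore mainly observed balance and gait.

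**3. Possible size.** The article gives no figure to reproduce on this point, so this is an illustration.

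Inputs:
- true risk of at least one fall: p = 33% in both groups (Background), so the true relative risk is 1
- share of fallers identified by the calls: s1 in visibly unstable participants, s0 in the others. Both are **assumed**; the article gives no such rates.

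Observed RR = (p × s1) / (p × s0) = s1 / s0.

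- s1 = 95%, s0 = 85%: 0.33 × 0.95 = 0.314 and 0.33 × 0.85 = 0.281, so RR = 1.12.
- s1 = 90%, s0 = 85%: 0.33 × 0.90 = 0.297 against 0.281, so RR = 1.06.

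The second case also shows the effect of partial overlap. If only half of the unstable participants are called by someone who saw them tested, and those calls reach 95% while all others reach 85%, the average is 0.5 × 0.95 + 0.5 × 0.85 = 0.90, and the RR falls to 1.06.

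**4. Effect on the false-positive rate.** Take the planned 450 complete participants, assumed to split 225 and 225, and the stated 5% level, assumed two-sided. Use a two-proportion z-test with p1 = 0.33 × s1, p0 = 0.33 × s0, d = p1 − p0, p̄ = (p1 + p0)/2, and

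- SE0 = √[2 p̄(1 − p̄)/225]
- SE1 = √{[p1(1 − p1) + p0(1 − p0)]/225}
- P(reject) = Φ[(d − 1.96 SE0)/SE1] + Φ[(−d − 1.96 SE0)/SE1]

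| s1 v s0 (assumed) | Apparent RR | P(reject) under a true null |
|---|---|---|
| equal | 1.00 | 5.0% |
| 95% v 90% | 1.06 | 6.7% |
| 90% v 80% | 1.13 | 12.2% |
| 95% v 80% | 1.19 | 21.2% |

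For the 90% v 80% row: p1 = 0.297, p0 = 0.264, d = 0.033, SE0 = 0.0424, SE1 = 0.0423, which gives about 0.119 + 0.003 = 0.122.

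**The case against.** Several stronger readings are tempting, and the article does not support them.

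- **That the same people test and call.** A reader might infer this from students appearing in both tasks. The text shows a shared group only.
- **That the project manager tests participants.** The article describes briefing staff and arranging sessions, not testing.
- **That nothing separates the two roles.** This would be an inference from silence. Rosters and interview scripts are often left to a full protocol, which is not at hand.
- **That callers decide whether a stumble counts as a fall.** No adjudication role is stated, and the outcome is the participant's own report.
- **That no second source of falls can exist.** The limitations section mentions participants keeping a diary. The only log described elsewhere is for pedometer non-wear, so this is unresolved, not excluded.

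The size can also be contested. The elicitation rates are assumed, and applying the higher rate to every unstable participant is a worst case. The apparent relative risks are small beside the odds ratio of 2.9 that the Background cites for balance deficits, although that is a different measure and only a rough comparison.

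These objections limit how firmly the point can be put. They leave two things standing. The article goes beyond silence on staffing: it names the people on both sides and draws them from an overlapping group. And the safeguards it does describe are for confidentiality, which does not mask a caller who was present at testing.

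**Conclusion.** The point holds as a possible bias that a low-cost change would reduce, not as a demonstrated error. The staffing described permits unmasked ascertainment of an interviewer-elicited primary outcome, and no masking of callers to baseline results is stated. The exposure is mainly to the second main question, through visibly observed balance and gait; step count and force-plate sway are less affected.

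With 90% to 95% of visibly unstable fallers identified against 85% of the others, a null association would appear as a relative risk of 1.06 to 1.12. That range rests on assumed rates and, at its upper end, on the caller's knowledge operating throughout the unstable group. If callers already differ from testers and do not see baseline results, this route to bias is largely closed and only a clarifying sentence is needed.

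**What to change.** In the Data collection section, state that:

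- each call is made by someone who did not test that participant;
- the caller has no access to that participant's baseline results until the 12 months of follow-up are complete;
- the fall question is read verbatim from a fixed script.

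Where this is not possible, or calls have already been made, record who tested and who called for each participant, and list possible interviewer bias among the limitations. If callers are already separated from testers, one sentence saying so settles the matter.

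**Cost.** A call roster and a call sheet without baseline results, within the existing student team and with no extra staff. The downside is less scheduling flexibility and less personal continuity for participants.
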